## Abstract

**Background:**

There is a critical need for effective implementation of integrated healthcare systems for children with autism spectrum disorder (ASD). Children with ASD have many service needs, including the need to access effective mental healthcare, given high rates of co-occurring psychiatric conditions. Pediatric primary care is an ongoing point of healthcare that is well positioned to identify mental health concerns and facilitate linkage to mental health services for children with ASD. However, identifying mental health problems in children with ASD by primary care providers is complex, subject to being overlooked and may significantly vary based on primary care organizational characteristics. Efforts targeting integrated primary-mental healthcare implementation require a tailored approach for children with ASD.

**Methods:**

This mixed methods, community-partnered study will apply the Exploration, Preparation, Implementation, Sustainment (EPIS) framework (Aarons et al., 2011; Moullin et al., in press) to adapt and implement an integrated care model, “Access to Tailored Autism INtegrated Care” (ATTAIN), in pediatric practices within three diverse healthcare settings for children ages 4–18 years. Key inner context factors from the Exploration, Preparation, and Implementation phases of the EPIS framework will guide three objectives of this study: (1) to identify targets to improve mental health screening and linkage to mental health services in primary care for children with ASD, (2) to adapt integrated care procedures to facilitate identification of mental health problems and linkage to evidence-based care for children with ASD, and (3) to examine feasibility, acceptability, and uptake of the adapted integrated mental healthcare model through a pilot study in pediatric primary care.

**Discussion:**

Improving integrated mental healthcare for children with ASD could have a significant public health impact on mental healthcare access, child clinical outcomes, and reduction in healthcare costs. Results from this mixed methods study will inform selection of implementation strategies to conduct larger-scale implementation of tailored integrated mental healthcare for children with ASD that will ultimately help to address the high unmet mental health needs for these children.

## Background

There is a critical need for effective implementation of integrated healthcare services for children and adolescents with autism spectrum disorder (ASD) whose numbers are rapidly growing [1]. Children with ASD often have complex physical and mental healthcare needs that necessitate both pediatric primary care and specialty care services [2, 3]. The prevalence of ASD and co-occurring psychiatric conditions (e.g., disruptive behaviors, attention and hyperactivity problems, anxiety) is estimated at greater than 70% [4, 5]. However, studies have shown that 41% of these children with ASD and co-occurring mental health conditions have substantial unmet mental healthcare needs [6]. Timely identification of co-occurring psychiatric conditions and linkage to mental health services for children with ASD is imperative to facilitate appropriate treatment and behavioral improvements [7].

Pediatric primary care is a principal point of care for children with ASD, so it is an ideal setting for early identification and ongoing monitoring of mental health needs and linkage to needed mental healthcare [8, 9]. Implementation of integrated mental healthcare is a potential solution to targeting timelier mental health screening and service linkage for children with a known diagnosis of ASD who also have co-occurring mental health conditions requiring intervention. Integrated care is an umbrella term that can encompass many different care arrangements. For this study, we define integrated care as a team of primary care providers and mental health specialists collaborating with the patient-family unit to coordinate care [10]. Although integrated care is not standard in pediatric primary care, emerging support exists for integrated healthcare approaches for children with ASD to facilitate addressing unmet specialty healthcare needs, including those for mental health [6, 11]. Further, when caregivers perceive themselves as shared decision-makers—an important component of integrated care—they report greater satisfaction with their child’s care quality [12]. Overall, integrated healthcare approaches show promise in reducing unmet mental health needs for children with ASD.

There are many patient, provider, organization, and system-level challenges to implementing integrated mental healthcare for ASD. One major challenge is diagnostic overshadowing. This is the process by which a diagnosis such as ASD obscures or prevents the diagnosis and treatment of other comorbid physical and/or mental health problems [13–18]. Another major challenge is the way pediatric primary care itself is structured, with well-child appointments typically lasting 11–20 min or less. Many topics need to be covered during the visit [19]. This places a significant burden on the pediatric primary care provider and caregiver to efficiently and effectively identify mental health concerns. In addition to limited time in pediatric primary care appointments, caregivers report many barriers to accessing pediatric specialty mental health services such as few qualified providers/services to treat children with ASD who have other psychiatric problems, inadequate care coordination and communication between pediatricians and other specialty providers, and difficulty obtaining information about specialized services [6, 20–22]. These implementation challenges suggest the potential need for increased ASD-specific mental health training of primary care providers to promote successful identification of co-occurring psychiatric conditions and initiate the integrated care process for children with ASD. Integrated care models are ideally suited to the way to address these barriers to mental healthcare for families of children with ASD who require additional assistance in accessing mental health services [23, 24].

To date, there have been no studies that have tested the use of integrated mental healthcare models for children with ASD within real-world pediatric primary care settings. This may be in part because many adaptations would need to be made for children with ASD. For example, screening instruments may need to be adapted or carefully selected to accurately identify mental health problems in children with ASD that may require targeted mental health treatment. This may be important because (1) core symptoms of ASD may overlap with other non-ASD psychiatric disorders (e.g., anxiety) and (2) non-ASD psychiatric disorders may manifest differently in children with ASD (e.g., for a child with ASD and anxiety, this may manifest as increases in repetitive or sensory behaviors versus rumination) [25]. Another key component of integrated care for children with ASD would be an integrated electronic health record to facilitate the coordination of the many services and healthcare providers necessary for effective treatment. This includes improved interoperability of the electronic health record to competently facilitate information sharing between providers [26]. Finally, there would need to be additional service navigation support, facilitated by the electronic health record and/or dedicated staff, for mental health screening and linkage for children with ASD, which has been strongly recommended to help families of children with ASD access appropriate treatment services [27].

The Access to Tailored Autism INtegrated Care (ATTAIN) study is designed to address the need for systematically adapting and testing an integrated care model for ASD. The ATTAIN study is a mixed methods implementation study that uses screening and linkage practices from the broader pediatric literature as well as the literature on adult integrated care to adapt the process of integrated care for children with ASD and co-occurring mental health conditions.

## Implementation science conceptual framework and approach

This study applies the Exploration, Preparation, Implementation, and Sustainment (EPIS) framework [28, 29] to identify specific contextual factors to target when implementing ATTAIN in primary care settings*.* The EPIS framework was selected because it is a four-phase, prospective implementation framework that defines outer (i.e., system-level) and inner (i.e., organizational, provider, patient) context factors that may influence implementation and sustainment of a new practice in a clinical setting. Figure 1 details the targeted outer and inner context factors across each EPIS phase that are relevant to implementation of ATTAIN in this study and broader pediatric integrated care implementation efforts. The outer context is conceptualized as stable across phases of ATTAIN implementation while the inner context evolves over the phases and represent the specific targets of the study. The first three phases (shaded in Fig. 1) are the focus of this study.

**Fig. 1 Fig1:**
[figure not shown]
Application of the EPIS framework (adapted from [28]). Shaded components are the focus in this study

A key component within the EPIS framework and that is an essential implementation strategy within this study involves the inter-organizational relationships among stakeholders and entities. In this study, this is represented through community-academic partnership [30]. Specifically, community partnerships have been established with three primary care healthcare organizations in Southern California: (1) a linked health system with the largest pediatric primary care group in two Southern California counties, serving families with private insurance and Medicaid, (2) a private, for-profit integrated healthcare system that has a variety of payment systems including self-pay, employer-based private insurance, and subsidized programs, and (3) a federally qualified health center that serves a racially/ethnically/linguistically diverse and lower-income patient population along the US/Mexico border.

The “ATTAIN Advisory Group” will be developed to maximize the “fit” between ATTAIN and a range of pediatric primary care contexts. The ATTAIN Advisory Group includes stakeholders from the three healthcare organizations (described above) that serve children with ASD. The ATTAIN Advisory Group will be established at the outset of the study and meet regularly to guide study design choices, interpretation of results, implementation of findings in primary care settings, and evaluation of the collaborative process. The ATTAIN Advisory Group will include the principal investigator and approximately eight community stakeholders who represent pediatric and mental health providers, researchers, leaders, and caregivers of children with ASD.

Using key inner context factors from the EPIS framework, three objectives of this study will be pursued: (1) to identify targets to improve mental health screening and linkage to mental health services in primary care for children with ASD, (2) to adapt integrated care procedures to facilitate identification of mental health problems and linkage to evidence-based care for children with ASD, and (3) to examine feasibility, acceptability, and uptake of the adapted integrated mental healthcare model through a pilot study in pediatric primary care.

## Methods

The study design and methods are presented in the following sections by study aim.

### Aim 1

Aim 1 is to use a quantitative concurrent with qualitative (QUAN+QUAL) mixed methods design [31, 32] to identify targets to improve mental health screening and linkage to mental health services in primary care for children with ASD. Perspectives from organizational leaders, pediatric providers, and caregivers of children with ASD will be gathered to inform adaptations needed to tailor such practices for children with ASD.

#### Participants

In this study, the term “provider” indicates a practitioner or clinician, rather than an organization. Purposeful sampling will be used to maximize variation in perspectives and depth of information about mental health screening and linkage practices in primary care settings [33]. Twenty participants will be recruited from each of the three organizations (total *n* = 60). These participants will be organizational leaders in primary care (e.g., executive director, director of pediatrics department, primary care clinic lead), primary care providers (e.g., pediatricians, developmental behavioral pediatricians, nurse practitioners, case managers), and caregivers of children with a known ASD diagnosis who receive primary care at one of the three healthcare organizations. This target sample size was selected based on recommendations from mixed methods implementation and qualitative method research [33, 34] to pursue the mixed methods functions of convergence, complementarity, and expansion and achieve *a priori* thematic saturation (based on the EPIS framework).

#### Procedure

Recruitment will occur through several methods including in-person appearances at staff meetings and flyers posted in patient areas. Those who are interested in study participation will be asked to complete a study contact form that includes their preferred contact details to receive more information about the study activities (focus group and survey). Focus groups will occur on-site at each organization or at a convenient location. At least three focus groups per organization will be conducted based on participant type: (1) organizational/clinic/program leadership, (2) pediatric providers, (3) caregivers of children with ASD. Focus groups will take approximately one hour and participants will receive a $40 gift card for their participation. Surveys will be distributed using web-based software. The survey will take approximately 20 min to complete, and participants will receive a $20 gift card for their time.

#### Instruments

Data will be collected using a web-based survey (QUAN) and focus groups (QUAL). The content of the survey and focus groups will be designed to elicit data gathering about key inner targets from the Exploration and Preparation phases of the EPIS framework [28] shown in Fig. 1. There will be two versions of the web-based survey: primary care provider and caregiver. The provider/staff version will include items from the Geisinger Health System’s Primary Care Physician needs assessment survey [35] regarding current use of mental health screening and comfort identifying mental health problems in children with ASD. The caregiver version will include items from the National Survey of Children with Special Health Care Needs, Access to Care Questionnaire [36] related to experiences in coordinating and accessing mental health services. These surveys are available upon request.

There will be two versions of the focus group guide: primary care provider and primary care leader. The focus group guides will be designed to support a semi-structured approach to include pre-selected interview questions to promote active participation of participants who have experience with or directed perspectives on mental health screening practices in their pediatric primary care setting for children with ASD [37, 38]. Probes will be used as needed to explore issues in more depth. Focus group content was finalized with consultation from the ATTAIN Advisory Group and includes the following constructs: the mental health needs of children with ASD served in primary care, comfort discussing mental health in primary care appointments, current mental health screening and linkage to evidence-based mental health procedures, and needed adaptations to current procedures for children with ASD. These focus group guides are available upon request.

#### Analysis

Mixed-methods analytic approaches will be used to integrate the data and results across methods and used to examine convergence (i.e., do the two methods confirm or find similar results?), complementarity (i.e., do the two methods provide more depth of understanding of research questions?), and expansion (i.e., do the two methods provide insights beyond either method alone?) [31]. Both data methods will be triangulated to analyze convergence, to understand whether qualitative and quantitative data yield similar responses to specific questions. Finally, as recommended by Aarons and colleagues [31], qualitative and quantitative analyses will be integrated to examine whether focus group data contextualize targets assessed in survey data for the purpose of expansion [31, 32].

### Aim 2

Aim 2 is to adapt integrated care procedures to facilitate identification of mental health problems and linkage to evidence-based care for youth with ASD. The design of this aim is to capitalize on the collaborative process of the ATTAIN Advisory Group to use the findings from the first aim to refine the components of ATTAIN and prepare for the pilot trial in the subsequent and final aim of the study.

#### Participants

The ATTAIN Advisory Group will participate and aid in finalizing components of ATTAIN. The members of the ATTAIN Advisory Group include the principal investigator and approximately eight stakeholders who are pediatric and mental health providers, researchers, or leaders and caregivers of children with ASD.

#### Procedure

Results from the mixed methods needs assessment from the first aim will be discussed during a series of meetings of the ATTAIN Advisory Group to guide identification of adaptations and co-develop refinements needed for the ATTAIN model. The possible adaptations to the standard integrated health approaches might include (1) administration of a pre-appointment, mental health screening instrument such as the Pediatric Symptom Checklist-17 [39–42] that may need adaptation to effectively identify manifestation of mental health symptoms within the context of an ASD diagnosis, (2) pediatric provider training to interpret and briefly discuss the screening results and rationale for a mental health referral over and above existing treatment services that the family may be receiving, (3) use of the electronic health record to facilitate a mental health referral for children with ASD who present with clinically elevated scores on the mental health screener, (4) tailored service navigation assistance to link families of children with ASD to mental healthcare, (5) access to evidence-based care (internal or external to the referring healthcare setting) that targets co-occurring mental health problems within the context of an ASD diagnosis, (6) electronic health record tracking of mental health appointment completion, and (7) collaboration between primary care and mental health providers for ongoing care. Meetings of the ATTAIN Advisory Group will occur on an approximately monthly basis, each lasting 1–2 h over 6 months. During each meeting, the ATTAIN Advisory Group will engage in a group discussion to review and refine drafted materials related to the ATTAIN model and implementation supports needed for the subsequent pilot study (Aim 3) in partner organizations. In these meetings, there will also be guided discussion about areas of the ATTAIN model and implementation supports that may require tailoring for primary care or mental healthcare settings (e.g., identifying alternative mental health referral mechanisms if an organization’s electronic health record limits changes to workflow structures)**.**

#### Measures

The collaborative process will be assessed by the ATTAIN Advisory Group Collaborative Process Survey (AIM Study; PI: [name]; [43]) that will be administered at the conclusion of each group meeting.

### Aim 3

Aim 3 is to conduct an open trial feasibility pilot test of ATTAIN (directly informed by adaptations identified in Aim 2) in pediatric primary care offices. The primary implementation outcomes that will be measured are ATTAIN feasibility, acceptability, uptake, and speed of implementation. In addition, two primary service outcomes will be measured: mental health services access and communication between primary care and mental health provider.

#### Participants

A total of 60 primary care providers will be recruited from primary care practices in the region. It is expected that 45 providers will agree to participate. This targeted sample size was chosen based on sample sizes used within completed pilot studies focused on service interventions in pediatric primary care [42]. Each provider will be asked to use ATTAIN with their pediatric patients who have a documented ASD diagnosis in the electronic health record over four consecutive months.

#### Procedure

Leadership at each primary care organization will be approached about their primary care practices participating in the pilot study. Primary care practices within each organization will be purposively selected for targeted recruitment of providers for ATTAIN implementation based on patient volume. Training in ATTAIN delivery will take place in advance of active implementation of ATTAIN. Subsequently, trained staff and providers will be asked to use ATTAIN with patients who have a documented ASD diagnosis during any outpatient appointment (e.g., annual check-ups, drop-in appointments) to maximize early detection of mental health problems and opportunity to link to mental health services. Quantitative data of ATTAIN use will be extracted from patient charts. After 4 months of ATTAIN delivery, participating providers and caregivers of youth with ASD with whom providers used ATTAIN will be asked to complete a brief online survey regarding their experiences using ATTAIN. Providers and staff will receive a $100 honorarium and caregivers will receive $20 for survey completion.

#### Measures

##### Feasibility and acceptability of ATTAIN

The Perceived Characteristics of Intervention Scale (PCIS) [44] will be used to examine providers perspectives regarding feasibility and acceptability of ATTAIN. The PCIS is a 20-item scale that assesses attitudes towards a specific intervention including relative advantage, compatibility, and complexity. Participants are asked to rate the extent to which they agree with each item on a 5-point Likert scale. Example items include, “The ATTAIN model is clear and understandable” and “Using the ATTAIN model fits well with the way I like to work.” Caregiver perspectives of feasibility and acceptability of ATTAIN will be measured using modified items from the caregiver web-based survey administered in Aim 1 and drawn from the National Survey of Children with Special Health Care Needs, Access to Care Questionnaire [36] .

##### Uptake

ATTAIN uptake will be measured using extracted data from the electronic health record system. Specifically, uptake will be defined as the proportion of ATTAIN-eligible patients (i.e., children with a documented ASD diagnosis) to the number children with whom providers used ATTAIN. Providers will be asked to self-report the patients with whom they used ATTAIN.

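### Uptake, a primary implementation outcome, is written with its ratio inverted, and its eligible count does not require the child to have had an appointment in the four-month window

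*Protocol article*

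**What the plan says.** The opening of Aim 3 in the protocol article gives uptake primary status: "The primary implementation outcomes that will be measured are ATTAIN feasibility, acceptability, uptake, and speed of implementation". The Uptake paragraph under Aim 3, Measures, says that uptake is "defined as the proportion of ATTAIN-eligible patients (i.e., children with a documented ASD diagnosis) to the number children with whom providers used ATTAIN". Its parenthesis gives the whole eligibility rule: "ATTAIN-eligible patients (i.e., children with a documented ASD diagnosis". The paragraph states no age limit, visit condition or time window.

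Three other places bear on who could have received ATTAIN:

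- The Methods part of the abstract places the model "in pediatric practices within three diverse healthcare settings for children ages 4–18 years".
- Aim 3, Participants, sets the period of use at four consecutive months for each provider.
- Aim 3, Procedure: trained staff and providers are "asked to use ATTAIN with patients who have a documented ASD diagnosis during any outpatient appointment".

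The Aim 3 Analysis section describes uptake across and between organizations, compares outcome measures between organizations by ANOVA, and fits linear regressions to find predictors of the primary implementation outcomes.

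**The concern.** There are two separate problems.

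**Direction.** A measure of uptake should rise with use and lie between 0 and 1. The written ratio does neither. If it were computed as written, a better-performing organization would score lower, and the sign of any association with a covariate would reverse. A unit with no use, which is highly informative for feasibility, would have no value.

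**Who counts as eligible.** Turning the ratio over makes the eligible count the denominator. A child with the diagnosis but no appointment during the four months would enter that denominator although the provider had no visit at which to use ATTAIN. The rate then mixes what providers did with how often children attended. The study relies on description and effect sizes, because the Limitations section says that it is not powered for significance testing. The uptake rate is therefore itself a result, and the Impact section says that the findings will inform a larger hybrid trial.

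**Working it through.** The article gives no uptake target, expected rate, visit frequency or age distribution, so there is no figure to reproduce. The check is arithmetic on the stated definition, and every input below is an assumption chosen for illustration.

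**Step 1: direction.** Let E be the number of eligible children and U the number with whom ATTAIN was used, with the U children among the E. The text gives E/U; an uptake rate is U/E. With E = 100 (assumed):

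| U | E/U, as written | U/E |
|---|---|---|
| 0 | undefined | 0% |
| 10 | 10 | 10% |
| 25 | 4 | 25% |
| 50 | 2 | 50% |
| 75 | 1.33 | 75% |
| 100 | 1 | 100% |

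The written quantity is never below 1 and falls as use rises.

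Averaging makes it harder to read. Take two providers with 10 eligible children each, one using ATTAIN with 1 child and the other with 9:

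- mean E/U = (10/1 + 10/9)/2 = 5.56
- pooled E/U = 20/10 = 2
- mean U/E = (0.1 + 0.9)/2 = 50%

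**Step 2: eligible count, after the inversion is corrected.** Let p be the share of children aged 4–18 and seen in the window with whom ATTAIN was used, s the share of diagnosed children seen, and a the share of diagnosed children aged 4–18. With s taken as the same at all ages, the rate over all diagnosed children is p × s × a. The rate over seen children in the age range is p.

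With p = 0.60 and a = 1:

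- s = 0.50: 0.60 × 0.50 = 30%
- s = 0.70: 0.60 × 0.70 = 42%

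Two organizations with identical provider behaviour but these two visit shares would differ by 42 − 30 = 12 percentage points.

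With p = 0.80 and a wider range of s:

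- a = 1: 0.80 × 0.30 = 24%, up to 0.80 × 0.90 = 72%
- a = 0.80: 0.80 × 0.30 × 0.80 = 19%, up to 0.80 × 0.90 × 0.80 = 58%

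Throughout the second set, use among seen children in the age range is 80%. Correcting the direction alone therefore leaves the reported rate open to a wide range that does not reflect provider behaviour.

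**The case against.** The strongest reply is that the inversion is a slip of wording. The sentence calls the measure a proportion and names it uptake, and only used over eligible fits both words. Both counts are collected either way. This stands. A reader might infer that the uptake data will be unusable, but the documents support only that the definition as written is unusable.

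A reader might also infer that zero-use providers will drop out as missing. The article does not say that uptake is computed per provider. A child-level indicator of use would leave nothing undefined, so that harm is conditional on the unit of analysis.

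On eligibility, it can be said that the abstract sets ages 4–18 for the whole study and that a measure need not repeat it. This largely stands, and the age limit is a clarification. It can also be said that the details of the record query belong in a fuller document, and that reach over all diagnosed patients is a legitimate measure. The second part stands. The first stands only in part, because the article does not leave eligibility open: it equates it with a documented diagnosis.

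Two further inferences go too far. The article does not say that ATTAIN can be used only at an appointment, and the Aim 2 Procedure lists a pre-appointment screener as a possible component. It also gives no visit frequency or age mix by organization. It describes differences in payer and population, so confounding of the organization comparison is possible but not shown.

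**Conclusion.** The point holds in two parts. First, the stated definition of a primary implementation outcome is inverted: at least 1 when the children with use are among those eligible, decreasing as uptake improves, and undefined where use is zero. This needs no assumption beyond the text. It is probably a wording slip and does not affect the data collected.

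Second, the eligible count carries no visit condition, although use is tied to outpatient appointments over four consecutive months. The dilution depends on figures that the article does not give. Under the assumed 60% use among children seen, the rate would read 30% to 42% if 50% to 70% are seen. Distortion of the between-organization comparison follows only if visit frequency differs between them, which is an assumption.

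**What to change.** Replace the definition with the following. Uptake is the number of distinct children aged 4–18 with documented ASD with whom ATTAIN was used, divided by the number of distinct such children who had at least one outpatient appointment with a participating provider during that provider's four-month period. If uptake is analysed by provider, a provider with such children but no use scores 0. The ratio over all diagnosed children may be reported beside it, labelled as reach. Measures of provider adoption, such as the share of trained providers with any use, are optional additions and not part of the correction.

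The cost is one sentence of text, plus visit date and age in the record extraction that Aim 3 already plans. The Trial status section reports that only Aim 1 enrollment had begun at submission. Settling the definition before Aim 3 data are extracted avoids choosing the denominator after the results are known.
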